## 5.0. SAMPLE SIZE

In the FIT trial [15], the mean baseline score was approximately 5.5 on the SPPB, however, participants were

## FRAILITY REHABILITATION: A COMMUNITY-BASED INTERVENTION TO PROMOTE HEALTHY AGING

recently discharged from inpatient units. In our geriatric outpatient clinic study, the mean baseline score was 6.3. Assuming baseline scores of approximately 6, we aim to improve or maintain group exercise and socialization scores (and not decline over time as it did in the FIT Trial control group) and achieve at least a 1.5 between-group difference with the multi-modal arm. **Improving SPPB scores by 1.3-points is substantial clinical meaningful change [54] and bringing scores above 7 represents an important functional difference [InCHIANTI study, scores below 7 were strongly associated with mobility disability which limits independence in the community [58]].** **Sample size (SPPB):** Assuming at least a 1-point difference at 6-month follow-up (e.g. SPPB= 6.5 in group exercise versus 7.5 in multi-modal, SD=2 based on FIT trial and our own pilot data), with alpha 0.05 and power of 90%, and factoring in a drop-out rate of 20%, we will need a total sample size of N=324 (108 per arm). **Sample size (Frailty):** Assuming at least a 0.05-point difference at 6-month follow-up (e.g. Frailty score 0.25 in group exercise versus 0.20 in multi-modal, SD=0.09 based on our CaMos study data [3], with alpha 0.05 and power of 90%, and factoring in a drop-out rate of 20%, we will need a total sample N=195 (65 per arm). **To achieve the power to examine both outcomes, we will target a total cohort of 324.**

In addition to examining important scientific questions related to the effectiveness of frailty rehabilitation and functional capabilities of older adults living with frailty, this study will examine whether frailty rehabilitation is a sustainable community-based model that decreases healthcare utilization. Significant societal benefits could be achieved if hospitalization and institutionalization can be postponed or avoided. Furthermore, with limited access to geriatric services, examining other models for supporting primary care providers in managing frailty patients are imperative.

### 6.0. ANALYSIS PLAN

The study statistician will analyze the study data and report it in accordance with the CONSORT criteria after data collection is completed. The analysis plan is described in **Table 3**. The **primary comparisons** are at 4-months. We will report between-group differences in, means or percentages, with 95% confidence intervals at the 4-month follow-up. All analysis will be an intention to treat. **Sensitivity Analyses:** 1) we will examine the per-protocol cohort (participants who completed the trial). 2) To examine the influence of covariates on our dependent variables including adherence, the generalized estimating equations (GEE) technique, assuming an autoregressive correlation structure, will be used to compare differences between intervention groups. GEE is a flexible tool to deal with correlated data (across multiple time-points) and appropriate for both continuous and dichotomous outcomes.

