### **Arm 1: Control:**

Participants randomized to the control arm will not receive any of the Frailty Management Interventions (see Table 1).

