**Table 3: Analysis Plan of Co-Primary Outcomes**

| Objectives                                                                                                                                                                                                               | Hypotheses                                                                       | Outcomes                                                                                                                   | Analysis                                |
|--------------------------------------------------------------------------------------------------------------------------------------------------------------------------------------------------------------------------|----------------------------------------------------------------------------------|----------------------------------------------------------------------------------------------------------------------------|-----------------------------------------|
| In community-dwelling older adults with frailty, does frailty rehabilitation (multi-modal and exercise only), compared with control (daily activity), improve physical function measured by physical performance? | Improved physical function with intervention; greatest effect in the multi-modal | SPPB (total score, sub-component scores) at 4-months
Sub-group:
Comparison b/w intervention groups; adherence | one-way ANOVA, post-hoc analysis
GEE |
| In community-dwelling older adults with frailty, does frailty rehabilitation (multi-modal and group exercise only), compared with control (daily activity), improve physical function measured by walking speed?  | Improved frailty status with intervention; greatest effect in the multi-modal    | 400m Walk Test (continuous) scores;
Sub-group:
Comparison b/w intervention groups; adherence                  | one-way ANOVA, post-hoc analysis
GEE |

**Economic analysis:** An individual-level economic evaluation alongside this trial will be done from the Ministry of Health perspective. We will examine changes in direct medical costs and effectiveness outcomes (e.g., quality-adjusted life years - QALYs), calculate and compare the ICER (e.g., \$/ QALY gained, \$/ a visit averted)[59] against a willingness-to-pay threshold (\$50,000/QALY)[60] to show if this program of frailty rehabilitation represents good value for money.

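### The two sensitivity analyses in section 6.0 are badly specified as checks of the intention-to-treat result: per-protocol means only completion, and the GEE group comparison takes in adherence

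*Protocol*

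**What the plan says.** Section 6.0 states "All analysis will be an intention to treat" and that the "primary comparisons are at 4-months". Table 3 gives the method for both co-primary outcomes as "one-way ANOVA, post-hoc analysis", with GEE listed in the same cell.

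Section 6.0 then lists two sensitivity analyses:

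1. "we will examine the per-protocol cohort (participants who completed the trial"; no attendance, intervention or deviation criterion is attached.
2. "To examine the influence of covariates on our dependent variables including adherence, the generalized estimating equations (GEE) technique", with an autoregressive correlation structure, which "will be used to compare differences between intervention groups".

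Table 3 also carries a sub-group line, "Comparison b/w intervention groups; adherence", and section 4.9 places adherence in sub-analyses.

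Section 4.7 describes the adherence data: the YMCA attendance record, and weekly log-books for home and group exercise, supplements, diet and vitamin D. On Arm 1, section 4.6 says "Participants randomized to the control arm will not receive any of the Frailty Management Interventions (see Table 1"). The All Arms text in the same section gives vitamin D3 to every arm, although Table 1 lists it among those interventions. The two statements need to be reconciled.

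**The concern.** A sensitivity analysis should change one questionable assumption of the primary analysis and show whether the conclusion survives. As worded, neither of these does that cleanly.

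The per-protocol set ignores the adherence data that the trial collects. It may contain much the same people as the primary ANOVA, in which case agreement between the two says little about non-adherence.

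The GEE sentence, on its natural reading, puts adherence into the model that compares the groups. Adherence is observed after randomisation and is plausibly driven by health. Adherence to classes, home exercise and supplements has no counterpart in Arm 1. Conditioning on it removes the protection of randomisation, yet the result would appear under the heading of sensitivity analyses and could be read as contradicting a real effect.

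**Working it through.** **1. The plan's own figure.** Section 5.0 gives a 1-point SPPB difference, SD 2, alpha 0.05, 90% power and 20% drop-out. Taking alpha as two-sided (the protocol does not say), n = 2 × SD² × (1.96 + 1.2816)² / d² = 2 × 4 × 10.51 / 1 = 84.1, so 85 per arm. Then 85 / 0.8 = 106.25, so 107 per arm (321). The t-based version needs 86, and 86 / 0.8 = 107.5, so 108 per arm and 324 in total. The stated size reproduces. Expected completers are 108 × 0.8 = 86.4 per arm, or about 259 of 324, leaving about 65 who do not complete.

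**2. Who is in the per-protocol set?**

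| Meaning of completed | Missing month-4 scores | Per-protocol against ANOVA set |
|---|---|---|
| Month-4 visit | Not imputed | Same people, about 86 per arm |
| Month-4 visit | Imputed | Differ by about 65 of 324; a completer analysis |
| Whole intervention, or the 6-month telephone follow-up | Either | Probably smaller, by an unknown number |

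The protocol does not say which row applies. None of the rows comes with a stated adherence criterion.

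**3. Adherence in a comparison with control.** Only the SD of 2 comes from the protocol. The other inputs are assumed:
- attendance has mean 0.75 and SD 0.20 in Arms 2 and 3, and is coded 0 throughout Arm 1;
- attendance has no causal effect on SPPB;
- attendance correlates r1 with underlying health, and SPPB correlates r2 with it;
- the true effects against control are 0.5 (Arm 2) and 1.5 (Arm 3).

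Arm 1 has no spread in attendance, so the slope comes from the active arms: b = r1 × r2 × 2 / 0.20. Each contrast with control shifts by −b × 0.75.

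| r1, r2 | b | Shift | Arm 2, Arm 3 by formula | Simulated |
|---|---|---|---|---|
| 0.3, 0.3 | 0.9 | −0.68 | −0.18, 0.83 | −0.15, 0.85 |
| 0.3, 0.5 | 1.5 | −1.13 | −0.63, 0.38 | −0.62, 0.39 |
| 0.5, 0.5 | 2.5 | −1.88 | −1.38, −0.38 | −1.38, −0.37 |

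With no correlation between health and attendance, the simulated estimates return to 0.50 and 1.49, which identifies the mechanism.

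**4. Arm 3 versus Arm 2.** The shift is −b × (mean attendance in Arm 3 − mean in Arm 2). With equal attendance it is 0, and in the table Arm 3 minus Arm 2 stays at 1.0. With b = 1.5 and Arm 3 attendance assumed 10 or 15 points lower, it is +0.15 or +0.225, so a true 1.0 becomes about 1.15 or 1.23. Simulation gave the same values.

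**5. If adherence carries the effect.** Assume instead that the effect is proportional to adherence, with no health confounding, adherence mean 0.75 and SD 0.15, and 86 per arm. The pooled slope is (0.5/0.75 + 1.5/0.75) / 2 = 1.33, and 1.33 × 0.75 = 1.0. The contrasts with control fall from 0.5 and 1.5 to about −0.5 and 0.5 (simulated −0.51 and 0.48). The standard error rises from 0.31 to 0.86, a factor of 2.8. Arm 3 minus Arm 2 stays at 0.99.

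**6. Limits.** These are single-time-point regressions, not the GEE over two visits. Section 6.0 does not say how adherence would enter. If it is missing rather than zero in Arm 1, controls drop out of the model and only step 4 applies. If it enters as a time-constant main effect and the arm effect is read from an arm-by-time term, the shift could be much smaller.

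**The case against.** The best defence is that the wording permits a harmless reading. In Table 3 the comparison between intervention groups is a sub-group item listed with adherence and set apart from the comparison with control, and section 4.9 also places adherence in sub-analyses. If the GEE contrasts only Arms 2 and 3, Arm 1 is not involved. That contrast, on which section 5.0 sizes the trial, is not distorted when adherence is alike in the two arms.

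This stands in part. It removes the problem of adherence that Arm 1 does not have, but the model still conditions on a post-randomisation variable. Arm 3 asks more of participants than Arm 2, so equal adherence cannot be taken for granted. Table 3 also lists GEE in rows whose objective is comparison with control, so the less favourable reading is not excluded.

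Two further points stand in full. The handling of missing month-4 scores may be set out in an analysis plan not shown here, so its absence is no fault. And section 6.0 never presents either analysis as a check on drop-out.

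A reader might infer more than the protocol supports:
- That the per-protocol and ANOVA sets are certainly identical. This needs both no imputation and completion meaning the month-4 visit.
- That Arm 1 can have no adherence at all. Under the All Arms text vitamin D goes to every arm, and its use is logged.
- That the GEE will reverse the sign of a real effect. This needs Arm 1 coded as zero, a particular model form, and assumed values for the other inputs.

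**Conclusion.** The point holds as a fault of specification in text that the protocol itself fixes. Defining per-protocol by completion alone leaves the set blind to adherence, and under the two conditions in step 2 it is the same roughly 86 of 108 per arm that the ANOVA uses. The GEE sentence, read naturally, puts a post-randomisation variable into a comparison of randomised groups.

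The illustrative size is a downward shift of about 0.7 to 1.1 SPPB points against control, for assumed correlations of 0.3 with 0.3 to 0.5 and Arm 1 coded zero. A stronger assumed correlation gives about 1.9. For Arm 3 versus Arm 2 the shift is zero with equal adherence, and 0.15 to 0.23 in the unequal cases tried.

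The primary estimate and the sample size do not change. What is at risk is how that estimate is interpreted, since these are the only two sensitivity analyses the protocol names. It should be corrected, but it does not undermine the trial.

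**What to change.** - **GEE.** Limit covariates in arm comparisons to baseline variables, such as the baseline score and the stratification factors (sex, age group, location preference). State which arms are compared.
- **Adherence.** Report it as a separate analysis within the active arms, labelled exploratory, and not as a sensitivity analysis of the randomised effect. A complier-average effect that uses randomisation as instrument for class attendance is not a ready substitute in Arm 3, because supplements, nutrition review and medication review can act outside the classes.
- **Per-protocol.** Define the set by an adherence threshold fixed before unblinding, using the attendance record and log-books, and say what the criterion is in Arm 1. Call the completion-based set a completer analysis, and say what completion means.
- **Arm 1.** Reconcile the two statements on vitamin D, so that it is clear which adherence data exist in that arm.

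The cost is protocol wording and a little more programming; the data are already being collected. The downside is a smaller per-protocol set that is still not protected by randomisation, so it should be reported as supportive only.

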**Table 3: Analysis Plan of Co-Primary Outcomes**

| Objectives                                                                                                                                                                                                               | Hypotheses                                                                       | Outcomes                                                                                                                   | Analysis                                |
|--------------------------------------------------------------------------------------------------------------------------------------------------------------------------------------------------------------------------|----------------------------------------------------------------------------------|----------------------------------------------------------------------------------------------------------------------------|-----------------------------------------|
| In community-dwelling older adults with frailty, does frailty rehabilitation (multi-modal and exercise only), compared with control (daily activity), improve physical function measured by physical performance? | Improved physical function with intervention; greatest effect in the multi-modal | SPPB (total score, sub-component scores) at 4-months
Sub-group:
Comparison b/w intervention groups; adherence | one-way ANOVA, post-hoc analysis
GEE |
| In community-dwelling older adults with frailty, does frailty rehabilitation (multi-modal and group exercise only), compared with control (daily activity), improve physical function measured by walking speed?  | Improved frailty status with intervention; greatest effect in the multi-modal    | 400m Walk Test (continuous) scores;
Sub-group:
Comparison b/w intervention groups; adherence                  | one-way ANOVA, post-hoc analysis
GEE |

**Economic analysis:** An individual-level economic evaluation alongside this trial will be done from the Ministry of Health perspective. We will examine changes in direct medical costs and effectiveness outcomes (e.g., quality-adjusted life years - QALYs), calculate and compare the ICER (e.g., \$/ QALY gained, \$/ a visit averted)[59] against a willingness-to-pay threshold (\$50,000/QALY)[60] to show if this program of frailty rehabilitation represents good value for money.

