| PRIMARY   | In community-dwelling older adults living with frailty and sarcopenia, does a 4-month multi-modal intervention (Arm 3) improve physical function (Short Physical Performance Battery and 400-m Walk Test) compared with control (Arm 1) and group exercise alone (Arm 2)?                                                                                              | HYPOTHESES: 
 
- Frailty rehabilitation will achieve the most successful results in frail and sarcopenic cohorts and offer enhanced benefits relative to the other arms. Socialization and exercise only will provide clinically meaningful improvements to physical function and frailty over time, with exercise alone achieving greater benefits than control (usual care).
 
- Frailty rehabilitation will result in greater reductions in healthcare utilization in frail and sarcopenic older adults relative to the other arms.
 
- A range of functional abilities and health-related quality of life will be identified in older adults living with frailty.
 
 |
| SECONDARY | To better understand the functional abilities (frailty; fear of falling; fitness; strength; cognition; health-related quality of life; life space mobility; activities of daily living; depression/mood; nutrition) of older adults living with frailty and sarcopenia and translate the first Canadian model of frailty and sarcopenia rehabilitation and management. |                                                                                                                                                                                                                                                                                                                                                                                                                                                                                                                                                                                                                                                                                                                                           |

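### The primary contrast differs between Section 2 and Table 3, and the one contrast that Section 5 sizes the trial on, multi-modal versus exercise alone, is listed in Table 3 as a sub-group item

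*Protocol*

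**What the plan says.** Three places in the Protocol bear on the primary contrast.

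- **Section 2.0, primary objective.** The multi-modal arm is to be "compared with control (Arm 1) and group exercise alone (Arm 2"). That gives two contrasts, Arm 3 versus Arm 1 and Arm 3 versus Arm 2, on SPPB and the 400-m walk.
- **Section 6.0, Table 3 (co-primary outcomes).** The SPPB row asks "does frailty rehabilitation (multi-modal and exercise only), compared with control (daily activity"), and the walking-speed row asks the same in nearly the same words. Whether the two active arms are pooled or taken separately is not stated. Under a Sub-group label, both rows list "Comparison b/w intervention groups; adherence". The analysis is a one-way ANOVA with post-hoc analysis, plus GEE.
- **Section 5.0, SPPB sample size.** The only contrast given is "SPPB= 6.5 in group exercise versus 7.5 in multi-modal, SD=2 based on FIT trial and our own pilot data". The remaining inputs are a significance level of 0.05, 90% power and a 20% allowance for participants lost; the result is 324 in total, 108 per arm.

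The SPPB outcome cell of Table 3 reads "SPPB (total score, sub-component scores) at 4-months". Table 2 and Section 4.8 name only SPPB and the 400-m walk as primary outcomes.

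**The concern.** Arm 3 versus Arm 2 is primary in Section 2.0, is the sole basis for power in Section 5.0, and is a sub-group item in Table 3. Arm 2 versus Arm 1 is absent from the primary objective but is part of Table 3's question. No later document can follow Section 2.0 and Table 3 together without overriding one of them.

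This contrast is the trial's stated reason for being. The Introduction faults an earlier multi-arm trial for lacking power to show that a multi-modal programme adds to its single components. As the tables stand, a positive Arm 3 versus Arm 2 result could be set aside as a subgroup finding. A result against control, or one on an SPPB sub-component, could be presented as primary. The stated 90% power belongs to one test on one outcome, so it carries over only if that test is the one treated as primary at the full 0.05.

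**Working it through.** **1. The contrasts side by side**

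| Contrast | Section 2.0 | Section 5.0 (SPPB) | Table 3 |
|---|---|---|---|
| Arm 3 vs Arm 1 | primary | not used | part of main question |
| Arm 3 vs Arm 2 | primary | only basis for N | under Sub-group |
| Arm 2 vs Arm 1 | not listed | not used | part of main question |

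No contrast has the same status in all three places.

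**2. Reproducing 324**

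Inputs from Section 5.0: difference 7.5 − 6.5 = 1.0, SD 2, alpha 0.05 (sidedness not stated; two-sided is what reproduces N), power 90%, drop-out 20%.

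- Normal formula: n = 2 × SD² × (1.960 + 1.282)² / difference² = 2 × 4 × 10.51 / 1 = 84.1, so 85 per arm.
- Two-sample t version: 86 per arm.
- Drop-out: 86 / 0.8 = 107.5, so 108 per arm, and 3 × 108 = 324.

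The figure reproduces exactly. It pays for one unadjusted pairwise test (Arm 3 versus Arm 2) on one outcome (SPPB).

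**3. Power of that contrast under other readings, 86 per arm**

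Standardised shift = 1 / (2 × √(2/86)) = 3.28. Power is about Φ(3.28 − critical value). The percentages below come from the t distribution or simulation.

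- Unadjusted 0.05: 90.3%.
- ANOVA gate, then unadjusted pairwise tests: 90% if the control mean is 6.0 and 88% if it is 6.5 (both means assumed).
- Tukey over three pairs, critical t 2.357: Φ(0.92), about 82%.
- Alpha 0.0125 (two contrasts × two outcomes): 77.4%.

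**4. False-positive chance if success on either co-primary outcome suffices**

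The correlation between SPPB and walking speed is not given in the Protocol and is assumed. The figures are simulated under no effect, with three arms and 86 per arm.

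- One outcome, ANOVA gate, three arms: 5% holds.
- Two outcomes, each gated by its own ANOVA: 9.2% at correlation 0.5 and 8.5% at 0.7. Over correlations 0 to 0.9 the range is 9.6% down to 7.2%. The ceiling for independent outcomes is 1 − 0.95² = 9.75%.

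If both outcomes must succeed, there is no inflation across outcomes, but joint power falls. It is about 84% for Arm 3 versus Arm 2, assuming the same standardised effect on the walk and a correlation of 0.5. Section 5.0 gives no figures for the walk test; its second calculation is for frailty.

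**5. Order of a fixed sequence on SPPB**

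- Arm 3 versus Arm 2 first at 0.05: 90% for that test, whatever the control mean.
- Arm 3 versus Arm 1 first: Arm 3 versus Arm 2 is confirmatory only if both steps pass. With an assumed control mean of 6.0 the first gap is 1.5 points, its power is 99.8%, and both steps pass about 90% of the time. With an assumed control mean of 6.5 both pass about 84% of the time.

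Section 5.0 aims to "achieve at least a 1.5 between-group difference with the multi-modal arm", but that sentence sets multi-modal against exercise and socialization, so it does not fix a control mean.

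**The case against.** Section 5.0 does not define a primary contrast. It gives an example difference, and sizing on the smallest expected gap is ordinary practice. That is fair: the direct contradiction is between Section 2.0 and Table 3, and Section 5.0 only shows which contrast the number of participants was built on.

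The Sub-group label may be a misnomer. No subset of participants is defined, both rows of Table 3 hypothesise the greatest effect in the multi-modal arm, and Section 6.0 speaks of primary comparisons in the plural. This supports treating Arm 3 versus Arm 2 as a main question, which is a reason to correct the label.

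The post-hoc method, the alpha split and the rule for success across two outcomes are commonly left to a statistical analysis plan, which is not at hand. Their absence here is no finding.

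A reader might infer that neither the 5% error rate nor the 90% power can hold, with error of 15 to 16% (two contrasts, two outcomes) or 20 to 21% (three contrasts, two outcomes). The Protocol does not support this. Those figures need ungated, unadjusted tests and an either-outcome rule. Table 3 specifies an ANOVA first, alpha 0.05 appears only in the sample-size paragraph, and no success rule is stated. The ANOVA is also a valid gate with three arms, so removing it would be a preference.

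**Conclusion.** The contradiction is real and stands on the page. Section 2.0 and Table 3 state different primary contrasts, and the contrast behind N = 324 is labelled a sub-group comparison. The placement of SPPB sub-component scores in the co-primary cell is a second, smaller conflict, with Table 2.

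The numerical consequence is conditional:

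- Arm 3 versus Arm 2 on SPPB total as the first or only primary test at 0.05: the stated 90% holds. The 5% also holds if it is the only test, or if later tests follow in a fixed order.
- Either outcome sufficient, ANOVA gate on each: error about 9% (correlation assumed 0.5 to 0.7), with power for the sized contrast roughly kept at 88 to 90%.
- Tukey: power for that contrast about 82%. Four-way split at 0.0125: about 77%.

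The document does not settle which of these applies. The point is that the primary hypothesis must be identified uniquely before results are seen.

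**What to change.** 1. State one primary contrast definition and use it in Section 2.0, Section 5.0 and both rows of Table 3. Say whether the active arms are ever pooled.
2. List Arm 3 versus Arm 2 in Table 3 as a primary comparison and take it out of the Sub-group line.
3. Make the SPPB sub-component scores secondary, in line with Table 2.
4. To keep the stated 90%, test in fixed order at two-sided 0.05: Arm 3 versus Arm 2 on SPPB total, then Arm 3 versus Arm 1 on SPPB total, then the 400-m walk in the same order of contrasts. If another scheme is preferred, restate the power in Section 5.0 at the adjusted level actually used.

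The cost is wording in the Protocol and in any analysis plan; N does not change under the fixed order. The downside is that a later test is not confirmatory once an earlier one fails. By comparison, restoring 90% under adjustment would take about 399 participants with Tukey (133 per arm) or 432 at alpha 0.0125 (144 per arm), by the normal formula with 20% drop-out.

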### 4.0. METHODS

**4.1. Design:** In this multi-arm RCT, 324 community-dwelling older adults (aged 65+) with frailty and at high risk for mobility disability will be randomized into one of three arms (**control, exercise only, multi-modal rehabilitation**) stratified by sex, age, and location preference. Rolling recruitment will occur with ten cohorts total (2-3 cohorts per site, n=33 participants per cohort), enrolled across the partner YMCA sites. Blinded assessors will assess clinical outcomes at 0 and 4-months, with an additional 6-months of healthcare utilization via telephone follow-up. The multi-modal intervention is adapted from protocols used in our prior pilot studies and designed to ensure safe training components for frail adults with an emphasis on improving functional ability.

**4.2. Recruitment Process:** Our team (Geras, McMaster University, and Hamilton Health Sciences staff, students/trainees, and volunteers) will collaborate with clinicians (e.g., physicians, nurses, physiotherapists, occupational therapists, case managers) and administrative staff/ services (e.g. HHS Hub) at Hamilton Health Sciences (HHS) (e.g. St. Peter’s Hospital, Juravinski Hospital, Hamilton General Hospital), McMaster University, and St. Joseph’s Healthcare Hamilton (SJHH) to identify potential participants from a variety of units. Additional sources of referral will be from any healthcare provider, including but not limited to, physicians, nurses, physiotherapists, occupational therapists, case managers, within Southern Ontario (external to HHS, McMaster, and SJHH). If requested/approved, these networks will also be provided with brochures, posters, and other study advertisements for recruitment.

A pre-screening referral form will be completed and sent to the research team to determine eligibility. If the referee is external to HHS/McMaster, the referee will be asked to sign a data transfer agreement prior to using

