**4.5. Randomization:** Stratified block randomization (1:1 randomization ratio) with the allocation sequence generated by a computer will be used to randomly allocate participants to their group assignment. Participants will be stratified based on their sex, age (<80 or  $\geq 80$  years), and location preference. Research staff will obtain informed consent and confirm eligibility and will randomize the participant using Research Electronic Data Capture (REDCap) randomization system, a secure web application for building and managing online surveys and databases. To protect against selection bias, the randomization sequence will be adequately concealed so that investigators/participants are not aware of the upcoming assignment. To protect against ascertainment bias, baseline measures will be assessed **prior** to randomization. Outcome assessors, the study biostatistician, the investigative team, and the steering committee will be blinded to intervention assignments. Research assistants, study intervention personnel (pharmacist, instructors) and participants will not be blinded.

**4.6. Interventions:** Participants will be randomized to one of three arms (control, group exercise only, multi-modal), with the intervention lasting 4-months (**Figure 1**). Each cohort will have at maximum, 11 people

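### The primary analysis of both co-primary outcomes is an unadjusted one-way ANOVA of 4-month values, which gives up precision by using neither the baseline measure nor the stratification factors

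*Protocol*

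**What the plan says.** Table 3 (Analysis Plan of Co-Primary Outcomes) has one row for each co-primary outcome. The SPPB row gives the outcome as "SPPB (total score, sub-component scores) at 4-months" and the walk row as "400m Walk Test (continuous) scores". In both rows the analysis entry is "one-way ANOVA, post-hoc analysis", with GEE on the next line of the cell.

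Section 6.0 puts the primary comparisons at 4 months and says: "We will report between-group differences in, means or percentages, with 95% confidence intervals at the 4-month follow-up". It lists GEE as the second of two sensitivity analyses, with this purpose: "To examine the influence of covariates on our dependent variables including adherence, the generalized estimating equations (GEE) technique". Adherence is the only covariate named. Neither the baseline value nor a stratification factor is mentioned.

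Section 4.1 states "Blinded assessors will assess clinical outcomes at 0 and 4-months", and randomisation is "stratified by sex, age, and location preference". Section 4.5 repeats the factors ("Participants will be stratified based on their sex, age" and location preference), splits age at 80 years, and places the baseline measures before randomisation.

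**The concern.** A one-way ANOVA has a single factor, here the arm. Naming it as the primary method therefore settles that nothing else enters the model. This is a stated choice and not a detail left open for a statistical analysis plan: a plan that adjusted the primary analysis would depart from Table 3.

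Two kinds of information are left out.

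- **Baseline value.** Baseline SPPB and walking speed are likely to be the strongest predictors of their own 4-month values. Without them, the residual variance is larger than it need be, and a chance difference between arms at baseline carries over in part into the reported effect.
- **Stratification factors.** Stratified randomisation makes the arms more alike on sex, age group and location. If these factors predict the outcome, a model that ignores them does not credit that balance, and its standard error is too large.

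At stake are wider confidence intervals and lower power than the collected data can support, in a trial whose main question includes multi-modal care against exercise alone.

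**Working it through.** **Inputs.** From Section 5.0: SPPB difference 1 point, SD 2, alpha 0.05, power 90%, drop-out 20%, N = 324 (108 per arm). The test is assumed two-sided, since the protocol does not say. The correlation between the baseline and 4-month values (rho) is not given either, so it is an assumption, shown over a range.

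**Step 1: reproduce the plan's figure.** A two-sample t-test with standardised difference 1/2 = 0.5 needs 85.03 completers per arm, rounded up to 86. Then 86/0.80 = 107.5, rounded up to 108 per arm, and 3 × 108 = 324. The stated N is reproduced exactly. It rests on the raw SD of 2, with no credit for baseline, so sample size and planned analysis agree. Power with 86 per arm is 90.3%.

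**Step 2: precision of the unadjusted analysis.** SE of a difference between two arms = 2 × √(2/86) = 0.305 points. The 95% half-width is 1.96 × 0.305 = 0.60 points.

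**Step 3: effect of adjusting for baseline.** Residual SD = 2 × √(1 − rho²). The variance falls by the fraction rho², and the interval narrows by 1 − √(1 − rho²). The sample that would give the same precision unadjusted is 86/(1 − rho²) completers per arm.

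| rho (assumed) | Variance reduction | SE | 95% half-width | Interval narrower by | Power for 1 point | Equivalent completers per arm |
|---|---|---|---|---|---|---|
| 0 (as planned) | 0% | 0.305 | 0.60 | 0% | 90.3% | 86 |
| 0.3 | 9% | 0.291 | 0.57 | 5% | 93% | 95 |
| 0.5 | 25% | 0.264 | 0.52 | 13% | 96.4% | 115 |
| 0.7 | 49% | 0.218 | 0.43 | 29% | 99.5% | 169 |

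The difference detectable with 90% power falls from 0.99 points as planned to 0.86 at rho 0.5 and 0.71 at rho 0.7.

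**Step 4: size of an ordinary chance imbalance.** If the SD at baseline is also 2 (an assumption), the SE of the baseline difference between two arms is again 0.305. With equal SDs the regression slope equals rho, so a one-SE imbalance moves the unadjusted estimate by 0.5 × 0.305 = 0.15 to 0.7 × 0.305 = 0.21 points, against a 1-point target. This is the loss in Step 3 seen in a single trial, and is not to be added to it.

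**Step 5: does the extra power matter?** The 90% applies to one contrast at alpha 0.05. The primary objective in Section 2.0 has two contrasts (Arm 3 against Arm 1 and against Arm 2), and Table 3 plans post-hoc comparisons without naming a procedure. As an illustration only, Bonferroni over three pairwise contrasts (alpha 0.05/3 = 0.0167) gives 80% power unadjusted, 91% at rho 0.5 and 98% at rho 0.7.

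**Not quantified.** The protocol gives no figures on how strongly sex, age or location predict the outcomes, so no size is put on the loss from the strata. Section 5.0 has no sample-size calculation for the 400-m walk, so all figures above are for SPPB.

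**The case against.** **GEE is already in the cell.** Outcomes are measured only at 0 and 4 months, so a GEE over multiple time points could use the baseline value, and its covariates may be set in a statistical analysis plan that is not shown. That is possible. But Section 6.0 classes GEE as a sensitivity analysis and names only adherence, which arises after randomisation. It does not change the primary estimate.

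**The planned analysis is valid.** This stands. A reader might infer that the unadjusted ANOVA is biased or the trial underpowered. The documents support neither. Under randomisation the unadjusted comparison is unbiased, its standard error already allows for chance baseline imbalance, and N = 324 delivers the stated 90% for one SPPB contrast. Ignoring prognostic strata makes the analysis conservative, not too liberal.

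**The size is unknown.** This stands too. It is tempting to say that a quarter to a half of the precision is lost. That holds only for rho between about 0.5 and 0.7, and it refers to variance. At rho 0.3 the share is 9%, and interval width changes much less than variance throughout. Likewise, the standard error is too large for want of the strata only if the strata are prognostic.

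**The walk baseline may be incomplete.** Section 4.4 requires the ability to walk only 25 metres, so some participants may not complete 400 m at baseline. An adjusted model needs a rule for them. This is a fair cost, and the fix covers it.

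**Conclusion.** The point holds as a matter of efficiency. The protocol fixes a primary analysis of both co-primary outcomes that leaves out the baseline value and the three stratification factors, all of which the trial already collects. The analysis is valid and meets its own power target, but it is less precise than it could be and leaves chance baseline imbalance in the estimate.

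For SPPB, with 86 completers per arm, the variance given up is 9% to 49% for a correlation of 0.3 to 0.7, or intervals 5% to 29% wider than needed when measured as the narrowing that adjustment would bring. The reading of the text is firm; the size depends on a correlation that the protocol does not state. The direction should be the same for the 400-m walk, but its size cannot be worked out from the document. The change should be made, though the trial would not be invalid without it.

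**What to change.** In Table 3, replace the one-way ANOVA as primary analysis of each co-primary outcome with a linear model: either ANCOVA of the 4-month value or a constrained longitudinal model on baseline and month 4. Include arm, the baseline value of the same outcome, sex, age group (under 80, 80 and over) and location. Report adjusted mean differences with 95% confidence intervals for Arm 3 against Arm 1 and Arm 3 against Arm 2.

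Keep the unadjusted ANOVA and the adherence GEE as sensitivity analyses, and label them so in Table 3 as well as in Section 6.0.

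State how a missing or incomplete baseline 400-m walk is handled. ANCOVA needs an explicit rule for such participants; the constrained longitudinal model treats baseline as an outcome and so keeps them.

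The cost is wording in Table 3 and in any statistical analysis plan, plus that one handling rule. No new data and no more participants are needed. The change should be made before unblinding, so that the choice of covariates cannot depend on the results.
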